### Interim analyses {21b}

As the primary endpoint is overall survival, reasonable follow-up time is necessary to evaluate this endpoint. When reaching 50% of inclusions, an interim analysis would not provide any information on the efficacy or futility of a recurrence-focused surveillance strategy since the corresponding information on overall survival of the patients included so far is still very limited. Therefore, no interim analysis was conducted.

### Methods for additional analyses (e.g., subgroup analyses) {20b}

The association between recurrence-focused postoperative surveillance, with subsequent detection of (a)symptomatic PDAC recurrence, and overall survival is anticipated to be at least partly mediated by the administration of treatment for recurrence (Fig. 3). To confirm this, we will perform a sub-analysis in which we stratify for recurrence treatment. As PDAC is known to be a highly heterogeneous disease, the underlying tumor biology might also influence the occurrence of (a)symptomatic disease recurrence and subsequently impact survival. To determine which part of the effect is mediated through recurrence-focused treatment (indirect effect) and which part can be attributed to tumor biology (direct effect), a causal mediation analysis will be performed to decompose the total effect. This will provide us further information on the true value of additional treatment for recurrence.

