### Objectives {7}

The main objective of this study is to investigate whether recurrence-focused surveillance with three-monthly serum tumor marker testing and computed tomography (CT) imaging improves survival of patients with primary resected PDAC.

We hypothesize that patients who receive recurrence-focused surveillance will be diagnosed with PDAC recurrence at an earlier stage (i.e., localized disease and a good performance status). This hypothetically increases the number of patients that could tolerate (experimental) treatment for recurrence, with subsequent potential survival benefits. The goal of recurrence-focused surveillance will therefore be to improve overall survival.

The secondary objectives of this study are as follows:To evaluate the impact of recurrence-focused surveillance on quality of lifeTo evaluate compliance to a recurrence-focused surveillance strategyTo evaluate the impact of recurrence-focused follow-up on worry of cancer recurrenceTo evaluate disease-free survivalTo assess clinical and radiological patterns of PDAC recurrenceTo assess the role of serum tumor marker testing in detecting recurrent PDACTo assess eligibility for recurrence-focused (experimental) systemic and/or local treatmentTo evaluate reasons to refrain from treatment for recurrence (i.e., eligibility, deteriorated condition, patient’s wish, doctors’ advice, etc.)To assess patients’ tolerance for treatment for recurrenceTo assess prognostic factors for asymptomatic PDAC recurrenceTo calculate the cost-efficacy of a recurrence-focused follow-up

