### Outcomes {12}

The primary outcome is overall survival, defined as the time from the date of PDAC resection until the date of either death from any cause or last follow-up.

Secondary outcomes are the following:Patient-reported quality of life and worry of cancer recurrence, as measured by PROMs questionnaires within the PACAP-PROMs and PACOPS project: general EORTC QLQ-C30 and EQ5D-5L, pancreas-specific EORTC QLQ-PAN26, HADS, and WOPS.Compliance to recurrence-focused surveillance, measured as the percentage of patients that either accepts or refuses participation in the intervention-arm, i.e., is willing to undergo recurrence-focused follow-up.Disease-free survival, defined as the interval between the date of PDAC resection and the date of first radiological signs of recurrence, or last follow-up if recurrence is not observed. Preferably, recurrence is proven by a biopsy showing pathological confirmation of recurrent PDAC. However, recurrence can be clinically confirmed with growth of a suspicious lesion on consecutive CT scans and elevation of CA 19–9 (> 37 U/ml) and/or activity on PET-CT following consensus in a multidisciplinary meeting.Clinical and radiological patterns of disease recurrence:◦ Asymptomatic recurrence is defined as PDAC recurrence detected by CT imaging during follow-up, in the absence of suspected symptoms. If PDAC recurrence is discovered due to a significant patient-initiated complaint that is new or has been increased in severity or frequency, disease recurrence is defined as symptomatic.◦ Localization of recurrence is categorized using five categories: (1) isolated locoregional recurrence: recurrence in the pancreatic remnant, locoregional lymph nodes, or surgical bed, such as soft tissue along the celiac or superior mesenteric artery, aorta, or around the pancreatojejunostomy site; (2) isolated distant recurrence: recurrence restricted to a single organ or site; (3) local + distant recurrence: simultaneous occurrence of both isolated locoregional recurrence and isolated distant recurrence; (4) multiple recurrence: recurrence at multiple distant sites; and (5) peritoneal carcinomatosis.The yield of CT surveillance and role of serum tumor marker testing in detecting PDAC recurrence, by calculating diagnostic accuracy values, i.e., sensitivity, specificity, positive predictive values, and negative predictive values.Eligibility for additional (experimental) treatment at time of recurrence diagnosis, based on the Eastern Cooperative Oncology Group (ECOG) or Karnofsky performance state, or inclusion criteria for study-related treatment of recurrence.Reasons to refrain from treatment for recurrence (i.e., non-eligibility, deteriorated condition, patient’s wish, doctors’ advice, progression during treatment, etc.).Patients’ tolerance to treatment for recurrence, measured by the reasons to stop treatment for recurrence (i.e., per protocol, deteriorated condition, patient’s wish, doctors’ advice, progression during treatment etc.).Morbidity associated with recurrence-focused treatment.Overall costs of recurrence-focused surveillance vs. costs as incurred with current non-standardized follow-up. Cost-effectiveness is examined through the EQ5D questionnaire and calculated using a Markov model.

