### Statistical methods

#### Statistical methods for primary and secondary outcomes {20a}

The latest version of R Studio will be used for statistical analysis.

Baseline characteristics will be reported using standard descriptive statistics. Success of randomization will be evaluated by eye-balling whether the distribution of baseline characteristics between the intervention and control group is even. Primary analysis will be performed according to the intention-to-treat principle. As such, patients randomized to the intervention arm of the trial who refuse recurrence-focused surveillance following the TwiCs design will be analyzed as part of the intervention group. The main study parameter is overall survival, measured as the time from the date of PDAC resection to the date of death. Patients are censored at the time of last known follow-up visit documented if no event occurred. Overall survival rates will be reported as median with 95% CI and will be calculated by the Kaplan–Meier survival curve method. Log-rank test will be used to compare survival between the intervention and control group. One- and 2-year survival probabilities will be calculated. Univariate Cox-proportional hazard analysis will be used to assess the crude effect of a recurrence-focused surveillance strategy on survival. In addition, adjusted effect estimates will be calculated using a multivariable Cox-proportional hazard model, including potential confounders for symptomatic PDAC recurrence. To address potential confounders for which the multivariable analysis needs to be adjusted, a Directed Acyclic Graph was designed on https://www.dagitty.net (Fig. 3). It is hypothesized that a recurrence-focused postoperative surveillance strategy leads to the detection of PDAC recurrence in an asymptomatic stage, which increases the probability to undergo treatment for recurrence, possibly improving survival. The association between postoperative surveillance strategy and overall survival is therefore fully mediated through presence of symptoms at the time of recurrence diagnosis and subsequent administration of recurrence treatment. Given that the median overall survival after resection of PDAC is 21 months and 1- and 2-year survival rates are 75% and < 50%, respectively, we expect that during our follow-up period at least 50% of included patients (*n* = 153) will experience an event. The number of variables included in the multivariable analysis is based on the rule of thumb of ~ 10 events per variable, where a categorical variable counts for the number of categories. Consequently, multivariable analysis is adjusted for 15 baseline covariates that are considered to be the most important, i.e., age (continuous), sex (male/female), and predictors that reflect an (un)favorable tumor biology or treatment course, including performance status (continuous), preoperative CA 19–9 value (continuous), tumor location (head/distal), resection margin status (R0/R1), tumor size (continuous), number of positive lymph nodes (continuous) and tumor differentiation (poor/well-moderate), and administration of adjuvant therapy (yes/no). Given that recurrence treatment is considered a mediator, and not a confounder, no adjustment for recurrence treatment is required. Because administration of neoadjuvant therapy is known to affect preoperative CA 19–9 values, resection margin status, tumor size, and number of positive lymph nodes, neoadjuvant treatment will not be adjusted for. Postoperative complications are deemed to affect the receipt of adjuvant therapy and will thus not be included in multivariable analysis. Results will be presented as hazard ratio’s (HR) with corresponding 95% confidence intervals (CI). A two-tailed *P-*value < 0.05 will be considered statistically significant.

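### The mediation analysis splits the surveillance effect through recurrence treatment alone; by the protocol's own causal account that split is not identified without further assumptions, and tumor biology cannot be the direct effect

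*Protocol article*

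**What the plan says.** Methods for additional analyses {20b} sets out to determine "which part of the effect is mediated through recurrence-focused treatment (indirect effect) and which part can be attributed to tumor biology (direct effect"). It then announces that "a causal mediation analysis will be performed to decompose the total effect. This will provide us further information on the true value" of treatment for recurrence. The same section describes the surveillance effect as "anticipated to be at least partly mediated by the administration of treatment for recurrence" and says that "the underlying tumor biology might also influence the occurrence of (a)symptomatic disease recurrence and subsequently impact survival".

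Statistical methods {20a} gives the causal chain. Surveillance "leads to the detection of PDAC recurrence in an asymptomatic stage, which increases the probability to undergo treatment for recurrence, possibly improving survival", and the association with survival is "fully mediated through presence of symptoms at the time of recurrence diagnosis and subsequent administration of recurrence treatment". The only adjustment set stated there is a list of baseline covariates for the Cox model.

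Three other sections describe the patient's state at recurrence. Objectives {7} expects that surveillance patients "will be diagnosed with PDAC recurrence at an earlier stage (i.e., localized disease and a good performance status"). The paragraph on recurrence diagnosis makes the offer of treatment depend on performance status and comorbidity. Outcomes {12} lists "Eligibility for additional (experimental) treatment at time of recurrence diagnosis, based on the Eastern Cooperative Oncology Group (ECOG) or Karnofsky performance state".

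**The concern.** Symptom and performance status at recurrence is affected by the arm, drives the treatment decision, and shares tumor biology as a cause with survival. It is therefore a confounder of the mediator-outcome relation that is itself affected by randomised allocation. In that setting the usual split into natural direct and indirect effects through treatment alone cannot be recovered without extra assumptions, and enrolling more patients does not help.

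The label on the remainder is a second problem. Tumor biology exists before randomisation and is balanced between arms in expectation. It can confound the relation between treatment and survival, but it is not a path from surveillance to survival.

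This analysis is meant to say whether treating early-detected recurrence explains a survival gain. The Discussion notes that guidelines lack recommendations on treating recurrence, and Dissemination plans {31a} says results may enter guidelines. A split that credits treatment with the better fitness of those who receive it could mislead on that question.

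**Working it through.** The protocol gives no figure for the mediation analysis, so there is none to reproduce. The check is structural, followed by an illustration in which **every coefficient is an assumption**.

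**1. Structure taken from the prose**

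- Arm → status at recurrence: {20a}, Objectives {7}.
- Status at recurrence → treatment: {20a}, the recurrence-diagnosis paragraph, Outcomes {12}.
- Tumor biology → status at recurrence, and tumor biology → survival: {20b}.
- Treatment → survival: the hypothesis in {20a}.
- Status at recurrence → survival other than through treatment: excluded by the full mediation in {20a}, left open by the partial mediation in {20b}.

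**2. When the split works.** With treatment as sole mediator and status omitted, it is recovered if (i) status acts on survival only through treatment and (ii) tumor biology is fully measured. {20b} looks for a direct effect, so it does not assume (i). For (ii), the baseline covariates in {20a} are proxies for what {20b} calls underlying biology in a heterogeneous disease.

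**3. Illustration A** (2 million simulated patients, no censoring, biology U unmeasured). A is the arm, L asymptomatic or fit at recurrence, M treated.

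- logit P(L = 1) = −0.6 + 1.5A − 0.8U
- logit P(M = 1) = −1.2 + 2.2L
- log T = 2.3 + 0.35M − 0.4U + error

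Treated: 42% of controls, 58% under surveillance. True indirect effect: 0.35 × (0.58 − 0.42) = 0.056. True direct effect: 0.

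| Analysis | Indirect | Direct |
|---|---|---|
| L omitted | 0.076 | (true 0) |
| L as an ordinary covariate in both models | 0.000 | −0.09 |
| Interventional: L-adjusted coefficient of M × arm difference in M | 0.055 | – |

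As survival-time ratios, exp(0.056) = 1.058 is reported as exp(0.076) = 1.079. With the coefficient of M set to 0, omitting L gives a false indirect effect of 0.02, or 0.042 if L also acts directly on survival (0.3). With a weaker biology-symptom link (0.4), the truth is 0.060 and the estimates are 0.072 (L omitted) and 0.000 (L as covariate).

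**4. Illustration B** (1 million patients, other assumed coefficients, a direct path from symptoms S to survival, treatment effect 0.30). True indirect effect 0.040, true direct effect 0.105.

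- S omitted, biology unmeasured: 0.068 and 0.074.
- S in both models, biology unmeasured: 0.000 and −0.120.
- S omitted, biology fully measured: 0.052 and 0.091, still biased because (i) fails.
- With no direct symptom path and biology fully measured: indirect 0.040, direct about 0. Both conditions of step 2 hold and the split is recovered.

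**5. Limits of the remedies.** The interventional estimate recovered the treatment path in each variant of illustration A. It does not cure biology that drives treatment directly: with such a path in illustration B, the same estimator gives 0.059 against 0.038. Treating symptoms plus treatment as one mediator block does worse. In illustration A it gives an indirect effect of 0.146 against 0.056, and a false 0.089 when treatment does nothing, because conditioning on symptoms opens a path between arm and unmeasured biology.

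**The case against.** The strongest reply is that {20b} promises only a causal mediation analysis. It names no estimator, natural-effect estimand, adjustment set or handling of symptoms, and a journal article may leave those to an analysis plan. That stands as far as missing detail goes. But the article does fix that treatment is the sole mediator, that the total effect is split, and that the remainder is tumor biology, and those choices cause the difficulty.

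A reader might infer more than the documents support:

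- **That the split is unidentifiable whatever is assumed, or certain to be biased.** It is not: under full mediation, as {20a} states, with biology fully measured, the bias vanishes.
- **That the protocol's diagram shows this.** Fig. 3 is not available here. The argument rests on the prose.
- **That the illustrated bias is the trial's bias.** The coefficients are assumed and illustration A has no biology covariates. Those in {20a} (CA 19-9, margin, size, nodes, differentiation) may be used in the mediation model. If they captured 25%, 50% or 75% of biology (assumed), 0.076 would fall to 0.071, 0.066 or 0.061.

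One could also read {20b} as taking mode of detection, not arm, as the exposure. Tumor biology would then confound the exposure, which still does not make it a direct effect.

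**Conclusion.** The concern holds in this form. By the causal account in {20a} and {20b}, supported by Objectives {7}, the recurrence-diagnosis paragraph and Outcomes {12}, the split through recurrence treatment alone is not identified without two further assumptions. One conflicts with the partial mediation stated in {20b} and the other is unlikely. The estimate is therefore likely biased, by an amount and in a direction the documents do not determine. The illustrations show that a treatment with no effect can acquire an apparent benefit, and that entering symptoms as an ordinary covariate can erase a real one.

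Two wording faults need no simulation: pre-randomisation biology is called a direct effect of surveillance, and full mediation in {20a} conflicts with partial mediation in {20b}.

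This is an additional analysis. The intention-to-treat log-rank and Cox comparisons of overall survival are untouched, so the change is worth making but does not bear on the main result.

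**What to change.** In {20b}:

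1. Replace the split by the interventional (randomised-analogue) indirect effect of recurrence treatment, estimated by g-computation or weighting. Model symptom status, performance status and site of recurrence at diagnosis as arm-affected intermediate confounders, and include the baseline biology covariates of {20a}.
2. Add a sensitivity analysis for unmeasured confounding of treatment and survival, since step 1 does not remove it.
3. Delete the label that equates tumor biology with the direct effect.
4. Reconcile the full mediation of {20a} with the partial mediation of {20b}.
5. Drop the claim that the analysis informs on the true value of treatment.

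Do not substitute a joint mediator block of symptom status plus treatment: it conditions on a collider when biology is not fully measured.

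The cost is revised wording and some more analysis work. Symptom status, site of recurrence and performance-based eligibility are already study outcomes. The downside is that interventional direct and indirect effects need not add up to the total effect, which should be stated in the report.

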**Fig. 3 Fig3:**
[figure not shown]
Directed acyclic graph to address potential confounders/effect modifiers to adjust in the multivariable analysis

Moreover, the time interval between diagnosis of recurrence and start of treatment for recurrence (directly after detection in case of asymptomatic disease recurrence or as soon as symptoms occur) might affect the outcome. We therefore will perform a sensitivity analysis in which we include this time interval as a time-varying covariate.

### Methods in analysis to handle protocol non-adherence and any statistical methods to handle missing data {20c}

Analyses will be performed according to the intention-to-treat principle. Patients who refuse the offered intervention (i.e., a recurrence-focused surveillance according to our study protocol) will therefore be analyzed as participating in the intervention-arm of the trial, although they receive a non-standardized, symptomatic follow-up. Moreover, despite that non-standardized surveillance in general results in a symptomatic follow-up strategy without routine follow-up imaging in daily clinical practice, a proportion of patients in the control arm will receive recurrence-focused surveillance based on shared decision-making. Since patient crossover might lead to effect dilution, our sample size is corrected for refusal in the intervention arm and agreement on routine imaging in the control arm. Besides the intention-to-treat analysis, a per protocol analysis will be performed of only those who strictly adhered to the protocol to estimate the true efficacy of the recurrence-focused follow-up strategy. Missing baseline data will be imputed using multiple imputation techniques. Both complete data analysis and multiple imputed data analysis will be performed to check for inconsistencies.

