### Who will take informed consent? {26a}

The inclusion and randomization process of the RADAR-PANC trial is schematically shown in Fig. 1. Potentially eligible subjects are identified by the (local) investigator or an authorized delegate, by checking pathology reports of patients with known or suspected PDAC after intended radical resection. The (local) investigator or an authorized delegate will confirm that a potentially eligible patient is included in the PACAP or PACOPS cohort and signed informed consent for being randomized in future studies according to the TwiCs design and participation in quality of life questionnaires. If not, the patient will continue standard of care and will not be randomized for this trial. If the patient meets all the eligibility criteria for the RADAR-PANC trial, the participant is randomized for postoperative surveillance strategy with a 1:1 allocation ratio. Participants are either randomized for follow-up according to the current, non-standardized practice (control), or recurrence-focused surveillance according to the trial protocol (intervention). If the patient is randomized to the control arm, no additional action is taken: patients will receive current standard of care and are not explicitly informed about being randomized to the control arm of the trial according to the TwiCs design. Patients randomized to the intervention arm of the trial will be approached by a researcher and will be offered the experimental intervention within the first 3 to 4 months post-surgery. These patients are informed that they are free to decide whether they want to accept or deny the intervention. Oral and written information is provided and the treating physician is informed. If the patient chooses to participate, the additional informed consent form is signed prior to the start of the intervention.

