**Fig. 2 Fig2:**
[figure not shown]
Kaplan–Meier curve comparing overall survival between patients with routine follow-up imaging and symptomatic follow-up in the Netherlands between 2014–2019 (unpublished data)

As we expect 80% of patients to accept the experimental intervention offered in the intervention arm of the study, an estimated refusal rate of 20% needs to be taken into account. This leads to a decrease of the overall survival to 29.4 months (80% × 32.0 months + 20% × 19.0 months) for patients in the intervention arm. Moreover, despite that current non-standardized follow-up in daily clinical practice mainly results in a symptomatic follow-up approach without routine imaging, data from our recurrence database showed that 85/1580 patients (5%) did nonetheless receive routine follow-up imaging based on shared-decision making (the remaining 199/284 patients (70%) who received routine follow-up imaging participated in a clinical study with a study-specific follow-up including routine imaging). This results in a slight increase of the suspected overall survival in the control arm to 19.7 months (95% × 19.0 months + 5% × 32.0 months). The clinically relevant survival difference of 29.4 months vs. 19.7 months for the intervention and control arm, respectively, also approximates the mean survival difference of 9.5 months presented in the meta-analysis from Halle-Smith et al. [33]. These numbers correspond to a relative hazard (RH) of survival of 1.49, which is used to calculate the sample size of the study. Furthermore, as we expect a minimal level of loss to follow-up in this surveillance study, a censoring rate of 1% is expected each month.

To detect a 49% overall survival improvement (RH of survival 1.49) for patients in the intervention group, as compared with the control group, with a statistical power of 80% and a 0.05 two-sided significance level, a sample size of 306 patients is required. This calculation was based on the assumption of an exponential model, a median overall survival of 19.7 months in the control arm, a follow-up duration of 30 months, a drop-out rate of 1% and a baseline event rate of 3.5%. Following this calculation, we plan to include 306 patients in total: 153 patients in the recurrence-focused follow-up group and 153 patients in the non-standardized, symptomatic follow-up group.

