### Recruitment {15}

To achieve adequate patient enrolment and reach the target sample size, all centers are encouraged to participate in the current trial. To ensure enrolment of all eligible patients, the study coordinator(s) are in close contact with the local investigators at the participating centers to obtain weekly updates about patients who underwent macroscopically radical PDAC resection. Eligible patients will be contacted by the study coordinators in consultation with the treating clinicians. If an eligible patient is not yet approached for participation in the PACAP or PACOPS project, informed consent for PACAP or PACOPS, including TwiCs and PROMs, will be discussed by the study coordinator(s).

In 2018, 2348 patients were diagnosed with pancreatic cancer in the Netherlands. About 20% (*n* = 470) of these patients underwent macroscopically radical (R0-R1) resection of the tumor. In the Netherlands, all pancreatic resections are performed in centers affiliated with the DPCG, which will all participate in the current study. Based on the current successful enrolment progress, we anticipate that 75% (*n* = 353) of all patients will be registered yearly in the PACAP cohort and that 80% (*n* = 282) of these patients will provide informed consent for the TwiCs design. About 150 patients each year are expected to be included in other studies with a study-specific follow-up, which is an exclusion criterium for the RADAR-PANC trial. This leaves 282 – 150 = 132 patients eligible for randomization in the current study each year. Fifty percent (*n* = 66) of patients will be randomized to a standardized surveillance strategy. We expect that 80% (*n* = 53) of these patients are willing to participate in the intervention arm of the study, with a participation rate of 100% (*n* = 66) in the control arm as a consequence of the TwiCs design. The expected time needed for inclusion of a total of 306 patients (153 patients in each arm) is therefore 28 months. The final analysis will be performed 30 months after the last patient is enrolled.

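### The per-protocol analysis of strict adherers cannot estimate true efficacy in this TwiCs design; a complier-average analysis with allocation as instrument is the better secondary estimate

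*Protocol article*

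**What the plan says.** The protocol article makes ITT primary in sections {20a} and {20c}. Patients who decline the offer stay in the intervention arm, "although they receive a non-standardized, symptomatic follow-up". Section {20c} then adds that "a per protocol analysis will be performed of only those who strictly adhered to the protocol to estimate the true efficacy" of the surveillance strategy. It does not say how strict adherence is judged in each arm, or whether controls who had routine imaging leave the set.

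The other relevant statements are these:

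- Sample size {14}: "As we expect 80% of patients to accept the experimental intervention offered in the intervention arm of the study", so that "an estimated refusal rate of 20% needs to be taken into account".
- Sample size {14}: 85 of 1580 patients (5%) in the Dutch database "did nonetheless receive routine follow-up imaging based on shared-decision making". Section {20c} also expects some controls to be surveilled.
- Informed consent {26a}: "If the patient is randomized to the control arm, no additional action is taken".
- Recruitment {15}: participation is put at 100% "in the control arm as a consequence of the TwiCs design".

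No complier or instrumental-variable analysis is mentioned.

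**The concern.** A per-protocol comparison keeps the protection of randomisation only if the same kind of patient is removed from both arms. Here the offer is made in one arm. Refusal is an observed event in the intervention arm and an unobserved trait in the control arm. Strict adherence has the same problem, because intervention patients have a schedule of eight rounds to keep and controls have none.

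At stake is the secondary claim about what surveillance does for patients who receive it. The ITT effect is diluted by design, so readers will look to this analysis for that answer. The plan tells them in advance that it provides it.

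**Working it through.** **Inputs from the protocol article.** Acceptance 80%, control-arm routine imaging 5%, medians of 32.0 and 19.0 months with and without surveillance, and 153 patients per arm (Sample size {14}); 28 months of accrual and final analysis 30 months after the last enrolment (Recruitment {15}).

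**Assumption not in the documents.** The ratio r of refusers' hazard to acceptors' hazard, varied from 0.5 to 3.

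**Step 1: the plan's own dilution.**

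- Intervention arm: 0.80 × 32.0 + 0.20 × 19.0 = 29.4 months, as stated.
- Control arm: 0.95 × 19.0 + 0.05 × 32.0 = 19.65 months, stated as 19.7.

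**Step 2: who is left.** Refusers in the intervention arm number 0.20 × 153 ≈ 31, leaving about 122 acceptors. The 153 controls contain a similar number of would-be refusers whom nobody can identify. About 0.05 × 153 ≈ 8 controls would have had routine imaging. Removing them takes out a different group.

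**Step 3: bias in 24-month survival with no true effect.** Let A be acceptors' survival and R refusers' survival. Acceptors minus all controls is A − (0.8A + 0.2R) = 0.2(A − R), which is zero only if A = R. Take r = 2 and a control median of 19.7 months. With x the acceptors' survival at 19.7 months, 0.8x + 0.2x² = 0.5 gives x = 0.5495 and a hazard of 0.0304 per month. Then A = 0.482, R = 0.233 and the bias is 0.2 × 0.250 = +5.0 points.

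**Step 4: simulation with no true effect.** 3000 trials, 153 per arm, 20% refusers, control median 19.7 months, 1% monthly censoring, administrative censoring at 30 to 58 months. Comparison of acceptors with all controls, unadjusted, two-sided 0.05.

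| r (assumed) | Per-protocol HR | Per-protocol rejection rate | Bias in 24-month survival (points) |
|---|---|---|---|
| 0.5 | 1.15 | 16% | −4.7 |
| 0.67 | 1.09 | 9% | −2.8 |
| 1 | 1.00 | 5% | 0 |
| 1.5 | 0.92 | 9% | +3.0 |
| 2 | 0.88 | 13% | +5.0 |
| 3 | 0.83 | 22% | +7.6 |

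ITT rejected in about 5% of trials throughout. A separate large-sample run gave per-protocol HRs of 0.96, 0.92 and 0.88 at r = 1.25, 1.5 and 2.0, with the ITT HR at 1.00.

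**Step 5: the complier estimate.** ITT difference divided by difference in receipt, on the plan's medians: (29.40 − 19.65) / (0.80 − 0.05) = 9.75 / 0.75 = 13.0 months, which equals 32.0 − 19.0. This is illustrative only, because medians do not mix linearly. In the simulation the complier estimate of the 24-month difference averaged about zero at every r. Its standard error was about 7.5 points, against 6.0 for the per-protocol contrast. Relative to ITT, the interval widens by 1/0.80 = 1.25 to 1/0.75 = 1.33.

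**The case against.** **Which patients are dropped.** A reader might infer that the plan trims the intervention arm alone. Section {20c} does not say so. Its preceding sentences describe crossover in both arms, so controls with routine imaging may also be excluded. That stands, and the table shows one reading only. It does not rescue the analysis, because would-be refusers remain among the controls on either reading.

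**Direction.** A reader might also infer that the bias must favour surveillance because sicker patients decline. The documents give no reasons for refusal and no prognosis of refusers. Section {11b} foresees participants too ill to attend, which makes a link between attendance and prognosis plausible. It does not describe patients who decline at the offer. Fitter refusers would reverse the bias.

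**Size.** The distortion is moderate. At r = 2 the spurious HR is 0.88, against a design effect of 1/1.49 = 0.67. With the 153 events expected in {20a}, significance needs an HR near exp(−1.96 × 2/√153) = 0.73.

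**Adjustment.** Section {20a} lists a multivariable model with performance status, CA 19-9, nodes, margin and adjuvant therapy. If applied here it could remove the part of the selection that these covariates capture. Section {20c} does not say that it will be, and unmeasured reasons would remain.

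**Compliance outcome.** Section {12} defines compliance as "measured as the percentage of patients that either accepts or refuses participation in the intervention-arm". A reader might treat this as a fault in the per-protocol set. No text builds the set on that outcome, which measures willingness; it is a separate labelling matter.

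**Conclusion.** The point holds as a fault in the purpose given to the per-protocol set. The design cannot identify comparable adherers in both arms, so the contrast is not an estimate of true efficacy unless adherence is unrelated to prognosis. With no true effect, the assumed range r = 0.5 to 3 gives per-protocol HRs from 1.15 to 0.83 and false-positive rates up to 22%. These figures assume 20% refusal, no covariate adjustment and all controls retained. Neither the sign nor the size can be fixed from the documents.

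ITT stays primary, so the primary conclusion and the sample size are unaffected. The harm is confined to the secondary efficacy claim. Since OS runs from resection and strict adherence becomes known only over the following 24 months, survivor selection is a further risk; it was not quantified.

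**What to change.** - Keep ITT primary.
- Make the secondary efficacy estimate a complier-average effect with allocation as the instrument. One form is the 24-month Kaplan-Meier survival difference divided by the between-arm difference in receipt of surveillance, with a bootstrap confidence interval. On the planning figures the divisor is about 0.80 − 0.05 = 0.75.
- Define receipt identically in both arms, from surveillance actually undergone. Acceptance of the offer is not enough. Section {11c} already has the coordinator track completed tests in the trial schedule; routine imaging in controls must be recorded to the same definition.
- State the assumptions. Under exclusion, allocation affects survival only through receipt; the plan's statement that refusers get ordinary follow-up makes this plausible but does not prove it. Under monotonicity, nobody is surveilled only if allocated to control. State also that the estimate applies to compliers only, about 75% of patients on the plan's figures.
- If the per-protocol analysis is kept, label it supportive and subject to selection bias, and delete the claim about true efficacy.

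The cost is a change of wording, a little more analysis work and an interval about 1.25 to 1.33 times wider than for ITT. No extra patients are needed for this change.
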